#### Psychological measures

##### Structured clinical interview for DSM-IV (SCID)

To examine the prevalence and the type of mental co-morbidity, the SCID interview, which consists of two parts, will be applied [69]. The SCID is a comprehensive and highly reliable and valid instrument [70]. The SCID-I is a semi-structured interview for the evaluation of major DSM-IV Axis-I diagnoses. With the SCID-I, it is possible to derive both a current and a previous history of psychiatric illness. The SCID-II procedure for assessing personality disorders (PD) is a two-stage process. First, subjects complete a 120-item questionnaire with questions based on the criteria from the DSM-IV. In the second stage, a semi-structured interview is administered. Positive answers must be re-evaluated by the interviewer to diagnose Axis-II PD. According to the SCID-II protocol, we will interview only those subjects who achieve the cut-off (a specified number of positive answers in a specific PD section) on the questionnaire [69]. All SKID interviews will be conducted by two psychologists with graduate training in clinical psychology. To ensure diagnostic reliability, all interviews will be audiotaped. One-fifth of the interviews will be randomly selected and rated by both psychologists. A kappa coefficient will be calculated to assess inter-rater reliability. Both psychologists will conduct 10 SKID interviews in a pilot phase. In cases of low inter-rater agreement further, training will be conducted by an experienced psychiatrist.

The *Hospital Anxiety and Depression Scale (HADS-D)* will be used to determine the severity of anxiety and depression. The HADS-D was especially developed for patients with somatic diseases and thus excludes physical symptoms. Each scale consists of seven items that measure anxiety and depression via the patient’s self-report with a four-stage response format. The HADS-D has good reliability (subscale depression: α = .81; subscale anxiety: α = .80) and validity [71].

##### Childhood Trauma Questionnaire (CTQ

The German Version of the CTQ will be used to measure early stress exposure. The CTQ measures maltreatment during childhood and adolescence and will be applied because it captures factors that are relevant to chronic pain [50] that are neglected by the SKID. The CTQ consists of five subscales (‘emotional abuse’, ‘physical abuse’, ‘sexual abuse’, ‘emotional neglect’, and ‘physical neglect’). Cronbach’s α ranges from .89 to .96, except for the subscale ‘physical neglect’ which yields an α of .62 [72,73].

##### 12-Item short form health survey (SF-12)

The health-related quality of life (HRQoL) will be measured with the SF-12. The SF-12 consists of 12 items on eight scales (‘physical functioning’, ‘role limitations due to physical problems’, ‘bodily pain’, ‘general health’, ‘vitality’, ‘social functioning’, ‘role limitations due to emotional problems’, and ‘perceived mental health’). Response categories vary from 2 to 6 and can be transformed to scale scores ranging from 0 (‘the worst’) to 100 (‘the best’) [74,75].

##### Resilience scale (RS-11)

Resilience is a personality characteristic that moderates the negative effects of stress and promotes adaption. Thus it avoids any potentially negative effects of stress. Resilience will be measured with the RS-11. The RS-11 comprises two factors – ‘acceptance of self and life’ and ‘personal competence’ – with a seven-point response format ranging from 1 ‘disagree’ to 7 ‘agree’. Thus, scores can range from seven to 77, with higher scores reflecting higher resilience. The RS-11 has very good reliability (α = .91).

#### Sociodemographic variables

Sex, age, education, employment status, marital status and further sociodemographic variables will by captured by a questionnaire.

### Measures of chronic pain mechanisms

We will determine whether the patient’s clinical manifestations of pain correspond with various specific potential pain mechanisms. In our study, potential mechanisms are captured through quantitative sensory testing (QST), the evaluation of conditioned pain modulation (CPM, the diffuse noxious inhibitory control-like effect), and analyses of nerve growth factor (NGF) plasma levels and endocannabinoid (ECs) profiles. Such potential mechanisms include peripheral sensitisation, central sensitisation, disinhibition, allodynia, and endogenous descending pain modulation.

#### Psychophysiological mechanisms

##### Quantitative Sensory Testing (QST)

Somatosensory function will be assessed using the comprehensive *QST* protocol developed as part of the German Research Network on Neuropathic Pain (DFNS). Seven tests measuring 13 parameters (warm detection threshold, cold detection threshold, thermal sensory limen, paradoxical heat sensation, cold pain threshold, heat pain threshold, mechanical detection threshold, mechanical pain threshold, mechanical pain sensitivity, dynamic mechanical allodynia, wind-up ratio, vibration detection threshold, and pressure pain threshold) [76] will be conducted. QST testing covers all relevant aspects of the somatosensory system including large and small fibre function as well as signs of central sensitisation (dynamic tactile allodynia, punctate mechanical hyperalgesia). This way, detailed profiles of somatosensory function will be obtained for the tested body areas. The test sites will be distributed throughout the paraspinal muscles (5 cm ± 0.5 cm next to the midline on the autochthon back muscles [L1 to S1]) and on the dorsum of the ipsilateral hand.

##### Conditioned pain modulation (CPM)

Inhibitory pain-modulating mechanisms will be assessed using the CPM, a diffuse noxious inhibitory control-like effect [77-79]. The difference in pressure pain threshold (PPT) before and after the induction of DNIC by phasic heat pain (PHP) will be measured. The appropriate temperature for PHP will be determined by measurement of the heat pain threshold (HPT). The PHP will oscillate ± 1°C around the PHP-temperature. The ratings of PHP pain intensity will be assessed using a computerised Visual Analogue Scale (VAS). The HPT will be obtained using ramped stimuli (1°C/s, 32°C baseline, 0°C and 50°C cutoffs, 8 cm^2^ thermode), which will be terminated when participants press a button. The mean of three consecutive measurements will be calculated. The PPT will be calculated as the mean of three consecutive measurements over the paraspinal muscles (5 cm ± 0.5 cm next to the midline on the autochthon back muscles [L1 to S1]; site contralateral to the QST).

#### Neurobiological measures

##### Nerve growth factor (NGF)

NGF levels in human blood samples will be determined using proximity ligand Elisa techniques. *Endocannabinoids (ECs)*: EC (anandamide (AEA), 2-arachidonoyl glycerol (2-AG), 1-arachidonoly glycerol (1-AG), palmitoyl ethanol amine (PEA), oleoyl ethanol amine (OEA), arachidonic acid) analyses of human blood samples will be performed by large-scale lipidomic profiling using the LC-MS/MS QTrap ABI5500. All analyses of NGF and ECs will be performed in collaboration with our consortium partners.

### Sample size estimation

A sample of more than 200 musculoskeletal pain patients (population-based sample and tertiary care sample) will be acceptable in order to recruit a sufficient number of “cases” with different clinical manifestations (e.g., local vs. generalised pain, different levels of pain affect, anxiety disorders, mood disorders, no mental comorbidity). To estimate the number of patients in different subgroups, we will refer to data from our population-based study. Approximately 61.8% of the patients in our population-based study had chronic local pain (CLP), and 38.2% had chronic widespread pain (CWP). We also found a prevalence of 12.7% for depression and 20.9% for anxiety disorders (using the SCID-I). The prevalence of depression and anxiety may be higher in a tertiary care pain setting, as reported by others [80,81]. Therefore, we expect group sizes that will be sufficient to gather abundant information regarding clinical manifestations. We also consulted recent QST studies and a review regarding DNIC to estimate the required group sizes. For DNIC testing, a systematic review [82] evaluated studies with an average group size of 20. A group size of 20 to 30 is also commonly used in recent QST studies [21,63,83]. We therefore expect our group sizes to be appropriate for the investigation of distinct sensory profiles. Studies investigating endocannabinoids used sample sizes between n = 10 and n = 20 patients per group and reported mean effect sizes between .60 and .80 (e.g. [84,85]). Studies with NGF have reported effect sizes between 2.02 and 4.31 [44,86]. With regard to pain mechanisms, small sample sizes are sufficient to compare subgroups. This will also apply for the groups of pain-free patients with PTSD, depression, and healthy controls (each n = 30, respectively).

### Quality assurance

To ensure that the measurements are reliable and high in quality, the project will have a pilot phase. In this pilot phase the study staff will be trained in the study procedures (if necessary) and conduct paired measurements to ensure reliability and validity. The pilot phase will be finished when the reliability and validity of the measurements has been verified. The study protocols will be tested and adapted if necessary.

### Statistical analyses

Descriptive statistics will be presented with means and standard deviations for continuous variables and absolute numbers and percentages for categorical variables. Questionnaires will be dealt with according to questionnaire manuals. The prevalence of chronic local pain, chronic widespread pain, fibromyalgia, and mental comorbidities will be determined for the population-based sample and tertiary care setting. Explorative cluster analysis will be conducted to establish subgroups based on the clinical manifestations observed. Therefore, the dimensions of pain (see above) and mental comorbidity will be used as cluster variables. Then, we will explore whether different neurobiological profiles (QST profiles, CPM, NGF levels, EC profiles) correspond with these subgroups. Pain drawings will be scanned, superimposed, and transformed into two-dimensional color-coded images. Body areas with high occurrence of pain will be illustrated in dark red; body areas without pain will appear in white. To classify patients who suffer chronic local pain (CLP) or chronic widespread pain (CWP), pain drawings will be analysed according to the ACR criteria [62] and a more precise definition [6]. Quantitative sensory testing (QST) data pre-processing and statistical analysis will be performed according to the protocol established by Rolke et al. [76]. To quantify conditioned pain modulation (CPM), the PPT before PHP will be subtracted from the PPT after PHP. Negative values indicate an analgesic effect due to CPM. Differences between patient groups will be analysed using analyses of co-variance (ANCOVA), followed by Fisher’s least significant difference test. Potential confounders will be included as covariates, if indicated. QST modalities or CPM will be entered as dependent variables, the patient groups as an independent variable. For more detailed information analysing QST data, we will refer to the protocol proposed by Rolke et al. [76]. The same procedure will be applied with regard to nerve growth factor (NGF) and endocannabinoids (ECs).

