The heterogeneity is supported by strong hints that subgroups exist that differ in terms of aetiopathology, clinical symptomatology, and psychophysiological patterns. A recent study revealed distinct somatosensory profiles in CBP and FMS: FMS patients showed increased sensitivity for different pain modalities in all measured body areas, which suggests central disinhibition (or a deficient pain inhibitory system) as a potential mechanism. CBP subjects, in contrast, exhibited localised alterations within the affected segment. Such alterations may be due to peripheral sensitisation [21]. This finding is in accordance with the main hypothesis of a mechanism-based diagnosis in chronic pain syndromes, which proposes that defined symptoms and signs reflect possible underlying neurobiological pain mechanisms [19,22]. Consequently, these subgroups should be treated with specific mechanism-based approaches, but to date, they have been treated with the same non-specific multimodal treatment programs. Therefore, the assessment of chronic pain and research identifying various factors associated with the development, maintenance, and spread of chronic pain, including their neurobiological correlates, is highly relevant.

Chronic pain has been found to be associated with a higher prevalence of mental co-morbidity. Patients with CBP [23,24], CWP [25], and FMS [26] suffer from mental disorders significantly more often than pain-free controls. This finding is especially true for anxiety disorders and mood disorders, which were found to have prevalence rates of 20.9% and 12.7%, respectively, in a population-based sample of patients with chronic back pain [23]. Of further interest is the role of psychological trauma, which has been neglected in previous research. Traumatic events have higher prevalence rates in patients with pain compared to pain-free controls or patients with other diseases [27-29]. Concerning traumatic experiences, it was suggested that multiple traumas have a cumulative effect on physical health, including back pain and that the impact of the trauma on health may be independent of post-traumatic stress disorder (PTSD) symptomatology [30,31].

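### CPM is scored only as a raw PPT difference, which can make a hypersensitive group look deficient in inhibition if inhibition is at least partly proportional to baseline; the stated sign rule also contradicts the formula.

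*Protocol article*

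**What the plan says.** The Statistical analyses section defines the outcome: "To quantify conditioned pain modulation (CPM), the PPT before PHP will be subtracted from the PPT after PHP". The CPM subsection of the Procedure agrees: "The difference in pressure pain threshold (PPT) before and after the induction of DNIC by phasic heat pain (PHP) will be measured". Neither normalises to the starting value.

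The sentence after the definition reads "Negative values indicate an analgesic effect due to CPM".

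The test stimulus is at the back: "The PPT will be calculated as the mean of three consecutive measurements over the paraspinal muscles", between L1 and S1, on the side opposite to the QST site.

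For group comparisons, "Differences between patient groups will be analysed using analyses of co-variance (ANCOVA), followed by Fisher’s least significant difference test". CPM is a dependent variable, and "Potential confounders will be included as covariates, if indicated". Baseline PPT is neither named nor excluded. The reference to an external protocol is worded for QST: "Quantitative sensory testing (QST) data pre-processing and statistical analysis will be performed according to the protocol established by Rolke et al. [76". CPM has its own formula.

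On expected sensitivity, the Background reports that "FMS patients showed increased sensitivity for different pain modalities in all measured body areas", and that chronic back pain showed local changes in the affected segment. Under Chronicity of pain, chronic status requires back pain on at least 45 days in three months. Controls must be pain-free on the test day.

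**The concern.** The section on measures of chronic pain mechanisms lists sensitisation and disinhibition as separate mechanisms. PPT serves both: it is one of the QST parameters, and it is the test stimulus for CPM. If baseline PPT differs between groups and the size of a threshold rise depends on baseline, a raw difference carries sensitisation into the measure of inhibition.

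The direction is awkward. The Background describes fibromyalgia as both hypersensitive and deficient in inhibition. A scale artefact would therefore look like confirmation of the prior expectation. At stake is whether a group's CPM profile is described correctly.

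Separately, the formula and the sign rule cannot both be right for a threshold, so a reader who applies the sign rule literally would reverse every CPM conclusion.

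**Working it through.** **Sign.** Take PPT 300 before and 360 after. After minus before = 360 − 300 = +60. The threshold rose, which is inhibition, yet the stated rule reserves analgesia for negative values.

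**No figure to reproduce.** The article gives no PPT value, unit, CPM effect, error size or alpha for CPM.

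**Inputs.** From the article: 30 per group (the size of each control group). Assumed: reference median PPT 400 units, between-person CV 35%, error CV of each PPT mean 5 to 15%, lognormal values, two-sided 5% test. True inhibition is the same in both groups: either proportional (+20%) or additive (+60 units).

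**Arithmetic.**
- Proportional: difference = 0.20 × baseline. 400 gives 80; 280 (30% lower) gives 56; 200 (50% lower) gives 40. The ratio is 1.20 each time.
- Additive: difference = 60 at any baseline. The relative rise is 60/400 = 15% but 60/200 = 30%, so here the ratio depends on baseline.

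**Simulated rate of a significant group difference** (1,000 runs per row):

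| True inhibition | Baseline gap | Error CV | Raw | Raw, baseline PPT as covariate | Log ratio |
|---|---|---|---|---|---|
| +20% | 30% | 5% | 71% | 8% | 6% |
| +20% | 30% | 10% | 32% | 9% | 5% |
| +20% | 30% | 15% | 18% | 16% | 6% |
| +20% | 50% | 5% | 100% | 9% | 4% |
| +20% | 50% | 10% | 77% | 18% | 5% |
| +20% | 50% | 15% | 47% | 31% | 5% |
| +60 units | 30% | 10% | 6% | 9% | 29% |
| +60 units | 50% | 10% | 3% | 19% | 87% |

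With equal baselines all three methods stayed between about 4% and 6%.

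**Why the covariate helps only in part.** The error in the first PPT enters both the covariate and, with opposite sign, the difference. The fitted slope is about (1 + k)ρ − 1, where k is proportional inhibition and ρ the reliability of PPT, ρ = ln(1 + 0.35²) / [ln(1 + 0.35²) + ln(1 + error CV²)].
- Error CV 5%: ρ = 0.979, slope 1.2 × 0.979 − 1 = 0.175, so 0.175/0.20 = 87% of the bias is removed (simulated gap −25.8 to −3.5 units).
- Error CV 10%: ρ = 0.921, slope 0.105, about half (−25.9 to −12.8).
- Error CV 15%: ρ = 0.839, slope 0.006, almost none (−25.4 to −25.3).
- Additive truth, error CV 10%: slope 0.921 − 1 = −0.079, so the covariate creates a gap where none existed (simulated −10.7 units at the 30% gap and −18.0 at the 50% gap).

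**Requiring both scales to agree.** Counting only significant results in the deficient direction, the raw difference alone was falsely positive in 17 to 100% of runs under proportional truth and about 7 to 78% under a mixture (+10% plus 30 units). Requiring agreement held this at about 3% or less under proportional, mixed and additive truth.

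**Price in power** (additive truth, error CV 10%, raw alone against both; 20,000 runs):
- Baseline 30% lower, inhibition a quarter of normal (15 against 60 units): about 85% against 67%.
- Baseline 30% lower, inhibition halved (30 units): 51% against 17%.
- Baseline 50% lower, inhibition halved: 58% against 3%, because 30/200 = 60/400 = 15% and the ratio sees no difference.

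**The case against.** The strongest reply is that this is a choice between two defensible scales. Nothing in the article shows that inhibition is proportional. If it is additive, the planned difference is unbiased and the log ratio errs in 29 to 87% of the simulated runs. That stands, and it rules out two stronger readings that a reader might infer: that the raw difference will necessarily make sensitive groups look deficient, and that the log ratio should replace it.

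A reader might also infer that low thresholds alone could generate a spurious disinhibition subgroup. They could not. Subgroups are formed by clustering clinical variables (pain dimensions and mental comorbidity), and CPM is compared across them afterwards.

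The ANCOVA allows confounders, and a condensed article may leave the covariate list to a fuller document. That is fair, but baseline PPT as a covariate is not a reliable cure, as shown above.

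Three further points stand. The size of any baseline gap is unknown. The PPT side is not stated to be the painful one. The design is descriptive and exploratory, with both PPT values recorded, so either scale remains available later. These limit the severity. They do not justify attaching a mechanistic label to one scale.

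**Conclusion.** The concern holds conditionally. The article fixes CPM as an un-normalised difference, expects groups to differ in sensitivity, and treats sensitisation and disinhibition as distinct. Under at least partly proportional inhibition, the raw difference can therefore mis-describe a hypersensitive group as deficient. In the simulations with fully proportional inhibition this happened in 17 to 100% of runs, depending on the baseline gap and measurement error. Under purely additive inhibition it does not happen beyond the nominal rate. The article does not say which applies, and every magnitude here depends on assumed PPT values.

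The sign contradiction needs no assumption: the formula and its interpretation disagree as written.

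**What to change.** 1. Keep the raw difference and add log(PPT after / PPT before) as a second CPM outcome in the same ANCOVA.
2. Describe a group as deficient in inhibition only if both outcomes show it. If they disagree, report the result as dependent on scale, not as normal inhibition.
3. State whether baseline PPT is a covariate, and do not rely on it as the sole correction.
4. Reconcile the formula and the sign rule. Either keep after minus before and let positive values mean analgesia, or reverse the subtraction and keep the present rule.

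The cost is one transformation and one extra analysis on data already planned, and two scales to report. The real price is power to declare deficient inhibition, which is modest when inhibition is nearly absent and large when it is only halved.

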**Physical examination**	
ACR Criteria for Fibromyalgia (ACR Classification) [62][102]	Tenderpoint count and documentation of specific symptoms
Physical Impairment Scale (PIS) [67]	Physical impairment (total flexion, total extension, average lateral flexion, straight leg raising, spinal tenderness, bilateral active straight leg raising, and sit-up)
Back Performance Scale (BPS) [68]	Disability. Tests of daily activities (Sock Test, Pick-up Test, Roll-up Test, Fingertip-to-Floor Test, and Lift Test)

* German Version.

**Table 2 T2:** Methods used to assess the potential mechanisms involved in chronic non-specific musculoskeletal pain

**Measures**	** *Variables* **
Quantitative Sensory Testing (QST) [76,103]	Comprehensive profiles of somatosensory functions (thermal and mechanical detection and pain thresholds, vibration thresholds, and pain sensitivity to sharp and blunt mechanical stimuli). Discrimination between local vs. generalised and peripheral vs. central nervous mechanisms.
Conditioned Pain Modulation (CPM, the diffuse noxious inhibitory control-like effect) [77,78]	A descending pain inhibitory mechanism that inhibits nociceptive activity arising from the afferent primary fibres at multiple levels of the dorsal horn, resulting in diffuse pain inhibition. These descending pain pathways originate from the brainstem and have significant inhibitory actions on nociceptive activity, thereby affecting pain perception.
*Blood Tests*	
Nerve Growth Factor (NGF)	Plasma NGF levels (proximity ligand ELISA techniques)
Endocannabinoids + related lipids (ECs)	EC (anandamide (AEA), 2-arachidonoyl glycerol (2-AG), 1-arachidonoly glycerol (1-AG), palmitoyl ethanol amine (PEA), oleoyl ethanol amine (OEA), arachidonic acid) in human plasma (large- scale lipidomic profiling using the LC-MS/MS QTrap ABI5500)
Genetics	2* 9 ml EDTA tubes, stored for the second funding period

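### The CPM score is defined as threshold after minus threshold before, yet negative values are said to mean analgesia; for a pain threshold the sign is the opposite

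*Protocol article*

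**What the plan says.** The Conditioned pain modulation section of the protocol article sets out the measurement: "The difference in pressure pain threshold (PPT) before and after the induction of DNIC by phasic heat pain (PHP) will be measured". The outcome is a threshold: "The PPT will be calculated as the mean of three consecutive measurements over the paraspinal muscles". The same section also collects visual analogue ratings, but only of the conditioning heat stimulus; they do not enter the score.

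The Statistical analyses section gives the formula and, in the next sentence, the reading: "the PPT before PHP will be subtracted from the PPT after PHP. Negative values indicate an analgesic effect due to CPM". The score is then used in the group comparison by analysis of covariance: "QST modalities or CPM will be entered as dependent variables, the patient groups as an independent variable".

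Table 2 describes CPM as a descending inhibitory mechanism, "resulting in diffuse pain inhibition".

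**The concern.** The formula and the reading conflict. Negative-means-analgesia is the right convention for a pain rating taken after minus before, or for a threshold taken before minus after. It is wrong for a threshold taken after minus before, which is what the section specifies.

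Direction is what CPM contributes to this study. The abstract names it as the measure of descending inhibition. The Background sets up the question in directional terms: inhibition was reported as deficient in fibromyalgia and normal in depressive disorder, and the wider literature is called inconsistent. If the stated reading is applied to the stated score, a subgroup with intact inhibition is reported as deficient, and the reverse. The Discussion also plans to repeat all the study's measurements before and after treatment in a feasibility trial, so the same misreading could carry over to the treatment effect.

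**Working it through.** No sample size, power or error rate is involved, so the check is of signs.

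**Inputs**
- Outcome: PPT, the mean of three consecutive measurements (Conditioned pain modulation section). A higher value means more pressure is needed to evoke pain.
- Direction of the mechanism: inhibition of pain (Table 2). Intact CPM should therefore raise the PPT.
- Formula: PPT before is subtracted from PPT after (Statistical analyses).
- Reading: negative means analgesia (Statistical analyses).

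**Derivation**
1. Subtracting A from B gives B − A, so CPM = PPT_after − PPT_before.
2. Analgesia means PPT_after > PPT_before.
3. Hence analgesia gives CPM > 0, and CPM < 0 means that the threshold fell.
4. The plan reads CPM < 0 as analgesia. Steps 3 and 4 contradict each other.

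**Illustration** (assumed values in arbitrary pressure units; the article gives none)

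| PPT before | PPT after | Score as defined | What happened | Plan's reading |
|---|---|---|---|---|
| 400 | 480 | 480 − 400 = +80 | threshold rose: analgesia | not analgesic |
| 400 | 370 | 370 − 400 = −30 | threshold fell: no analgesia | analgesic |

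**Readings that might rescue the text**
- *Reverse order, PPT_before − PPT_after.* Negative would then mean analgesia, but the text states the other order.
- *A pain rating as the outcome, after minus before.* Negative would again mean analgesia, but both sections name the PPT, and the only ratings mentioned concern the conditioning heat.
- *A PPT that is sign-reversed before subtraction.* The article refers to a cited protocol for sensory-testing data, but gives CPM its own formula in terms of the PPT and mentions no reversal.

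None of these makes the formula as written agree with the reading as written.

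**Effect on the analysis.** Replacing CPM by −CPM multiplies every adjusted group mean and every difference by −1. The F statistic, the p-values of the least significant difference test, the absolute differences and the power are unchanged. Cluster formation is also unaffected, since the cluster variables are the pain dimensions and mental comorbidity. Only the direction of interpretation changes.

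**Number affected.** 200 pain patients + 90 controls = 290 planned participants, if all undergo CPM testing.

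**The case against.** The strongest reply is about consequence, since the contradiction itself is not disputed.

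- *No test is affected.* CPM is a continuous dependent variable, with no responder cut-off by sign, in a study described as descriptive and exploratory. This stands, and it limits the damage to interpretation. It also means that the output gives no warning that the sign has been misread.
- *The harm is conditional.* The article does not show whether the slip is in the subtraction order or in the label. If the derivation actually used is before minus after, only the formula sentence is wrong and no value would be misread. This stands too: the wrong reading follows only if both sentences are applied as written.
- *CPM is not the only evidence on central mechanisms.* Quantitative sensory testing also bears on peripheral versus central processes, so a CPM sign error would conflict with that evidence and need not by itself overturn a conclusion about disinhibition. This is fair. What is reversed is the CPM result.
- *Absent inhibition is not a fall in threshold.* Absent inhibition gives a score near zero; a clearly negative score means facilitation or measurement noise. This is correct, and it does not alter the sign argument.

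None of these points reconciles the two sentences.

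**Conclusion.** The concern holds. The protocol article states a scoring rule that contradicts itself: as defined, a positive CPM score means analgesia, and the article says a negative one does. This is an explicit rule stated wrongly, not a detail left to a fuller plan.

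If the rule is followed literally, every non-zero CPM value is read backwards, in up to 290 participants. Error rates, power and the sizes of group differences are untouched. The conclusion rests on two things: that the PPT is kept on its natural scale, where higher means less sensitive, and that the subtraction is carried out as written. Nothing in the article departs from either. It should be corrected before CPM results are analysed or reported, because direction is the scientific content of this measure.

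**What to change.** Choose one of two equivalent repairs:
1. Keep PPT after minus PPT before, and state that positive values indicate an analgesic effect.
2. Define the score as PPT before minus PPT after, and keep the statement that negative values indicate an analgesic effect.

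The first leaves the formula as published and has the more natural reading, with larger values meaning more inhibition. Whichever is chosen, check it against the derivation code and use the same convention in the data set, tables, figures and any later use of the score in the feasibility trial. The cost is one sentence and a code check; no new data, sample size change or change of test is needed.

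### The ANCOVA stated for QST names patient group but no test site, so as written it does not directly test localised against generalised change

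*Protocol article*

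**What the plan says.** - **Purpose.** Table 2 of the protocol article lists, among what QST is to deliver, "Discrimination between local vs. generalised and peripheral vs. central nervous mechanisms". The Background supplies the motivating pattern. Fibromyalgia patients were more sensitive in all measured areas, which is read as central disinhibition. For chronic back pain it says: "CBP subjects, in contrast, exhibited localised alterations within the affected segment", with peripheral sensitisation as a possible reason.
- **Measurement.** The QST section describes "Seven tests measuring 13 parameters". On location it says "The test sites will be distributed throughout the paraspinal muscles" "and on the dorsum of the ipsilateral hand", with details of the back site in between. Both sites belong to the same person.
- **Model.** Under Statistical analyses, group differences are analysed by ANCOVA followed by Fisher's least significant difference test: "QST modalities or CPM will be entered as dependent variables, the patient groups as an independent variable". On further terms the section says only: "Potential confounders will be included as covariates, if indicated".
- **Delegation.** The same section refers twice to a cited QST protocol (reference 76) for how QST data are pre-processed and analysed. That source is not among the documents.

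**The concern.** Whether a change is localised or generalised is a question about a difference of differences: is the group difference at the back larger than the group difference at the hand? A model with group as its only named factor, applied to a QST modality, estimates a group difference. It contains no term for how that difference varies between sites.

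The back and hand values are paired within participants, so the data for a direct test will exist. Without a stated site contrast, a local-versus-generalised conclusion has no estimate or confidence interval behind it in the written plan. The Background ties this pattern to mechanism (peripheral sensitisation or central disinhibition), and the Discussion aims at a mechanism-based classification. An unsupported reading of site would carry through to that classification.

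**Working it through.** **1. The plan's own figure.** There is none to reproduce. Sample size estimation gives no alpha, power, SD or effect size for QST; it cites 20 to 30 per group by precedent. Its effect sizes of 0.60 to 0.80 are for endocannabinoids.

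**2. Structure.**

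| Element | Where | Content |
|---|---|---|
| Task | Table 2 | separate local from generalised |
| Data | QST section | 13 parameters, back and hand, same person |
| Stated model | Statistical analyses | group, plus unlisted covariates |
| Term that answers the task | not stated | group-by-site, or back minus hand |

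**3. Illustration: what if the two sites were read separately?** Assumptions, none from a QST figure in the article: two-sided alpha 0.05, 30 per group, between-site correlation ρ = 0.3 to 0.7, the same true shift d at both sites, and d = 0.6 or 0.8 borrowed from the endocannabinoid range.

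- Expected z at one site: d / √(2/n) = 0.6 / √(2/30) = 0.6 / 0.258 = 2.32.
- Power at one site: Φ(2.32 − 1.96) = Φ(0.36) = 0.64.
- Rough ceiling, if the sites were independent: P(back significant, hand not) = 0.64 × 0.36 = 0.23. Positive correlation lowers this.

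Simulation of the two correlated tests gives P(back significant, hand not). Ranges span normal and t-based calculation:

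| n per group | d | ρ = 0.3 | ρ = 0.5 | ρ = 0.7 |
|---|---|---|---|---|
| 30 and 30 | 0.6 | 19% | 16% | 12% |
| 30 and 30 | 0.8 | 10% | 8–9% | 6–7% |
| 20 and 20 | 0.6 | 20% | 17% | 13% |

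The opposite pattern (hand only) is equally frequent. A direct test of back minus hand keeps false site differences at 5%.

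**4. Larger groups.** If the 61.8% / 38.2% split of local and widespread pain in Sample size estimation held for all 200 pain patients (an assumption), there would be 0.618 × 200 ≈ 124 and 0.382 × 200 ≈ 76. For 124 against 76 at d = 0.6, the back-only pattern falls to about 1%. For 124 against 30 controls it is about 8 to 12% at d = 0.6 and about 2% at d = 0.8.

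**5. Power of the direct test.** Let the true shift be 0.6 SD at the back and zero at the hand, with 30 per group. The SD of the within-person difference is √(2(1 − ρ)).

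| ρ | SD of difference | Expected z | Power = Φ(z − 1.96) |
|---|---|---|---|
| 0.3 | 1.18 | 2.32 / 1.18 = 1.96 | 50% |
| 0.5 | 1.00 | 2.32 | 64% |
| 0.7 | 0.77 | 2.32 / 0.775 = 3.00 | 85% |

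With t-based calculation these are about one point lower (49%, 63%, 84%). For 80% power, n per group = 2(1.96 + 0.84)² × 2(1 − ρ) / 0.6², which is 62, 44 and 27.

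**The case against.** - **Reference 76.** The strongest reply is that QST analysis is twice referred to a cited protocol that may contain a site comparison, and that a condensed article may leave such detail to the full plan. This limits the point. A reader might infer that the final analysis has group as its only factor; the documents do not establish that. What stands is that the article writes out its dependent variable, independent variable and post-hoc test, and that model does not address the task set in Table 2.
- **Comparing significance.** A reader might also infer that localised change will be declared when the back is significant and the hand is not. No section states such a rule, or says that the sites are tested separately. The percentages above show what that reading would do; they are not error rates of the plan.
- **Importance.** The second objective asks whether sensory profiles differ between subgroups, which a between-group ANCOVA can address. Patients are classed as having local or widespread pain from pain drawings, not from QST, and the study calls itself exploratory. This is fair and lowers the weight of the point. Even so, an exploratory study needs an estimate of any contrast it interprets, and Table 2 names this one.
- **Size.** It would be tempting to multiply 12 to 19% by 13 parameters and announce 1.6 to 2.5 false localised findings per group comparison. That requires a true 0.6 SD shift at both sites in every parameter, which nothing in the article supports.

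**Conclusion.** The point holds in limited form. The stated ANCOVA names patient group and unspecified covariates only. Unless reference 76 supplies a site term, the written model gives no direct test of localised against generalised change, although Table 2 assigns that question to QST and the paired data will be collected. This conclusion rests on reading the text, not on a calculation.

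The size is an illustration under assumed inputs. With separate reading of the sites, a false back-only pattern would appear in about 12 to 19% of parameters (d = 0.6) or 7 to 10% (d = 0.8) at 30 per group, and less often in larger groups. Cluster sizes are not known in advance, so the figure for the subgroups of main interest cannot be fixed. The change is worth making, but the omission does not undermine the study's between-group comparisons.

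**What to change.** For each QST parameter, on the pre-processed values, fit one mixed model with group, site (back, hand), group-by-site and a random participant effect, plus the chosen covariates. An ANCOVA on the within-person back-minus-hand difference is an alternative. Base any statement that a change is larger at the back on that contrast with its 95% CI, and report the group estimates at each site beside it. If reference 76 already provides such a comparison, one sentence saying so and naming the term is enough.

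**Cost.** Some wording and a little more analysis work; no new data and no change to the examination. The real drawback is power: about 50 to 85% for a back-only shift of 0.6 SD at 30 per group under the assumptions above (49 to 84% with t-based calculation). The plan should therefore say that a non-significant interaction is inconclusive and is not proof of generalised change.
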